**17-2-1. Control Group**

In this group, participants will receive sensory-motor exercises combined with sham transcranial electrical stimulation for 4 weeks, three times a week (12 sessions). Participants will first receive the sham stimulation and then perform the exercises.

**17-2-2. Intervention Group**

In this group, participants will receive sensory-motor exercises combined with real anodal transcranial electrical stimulation for 4 weeks, three times a week (12 sessions). Participants will first receive the real stimulation and then perform the exercises.

**17-2-3. Sensory-Motor Exercises**

The goal of sensory-motor exercises is to enhance proprioceptive input from three areas (the soles of the feet, the sacroiliac joint, and the cervical vertebrae) to facilitate coordinated and automatic movement patterns. Therefore, maintaining the correct positioning of these three areas is essential throughout the exercises. To stimulate the foot receptors, exercises will be performed barefoot. Participants will then be asked to contract the muscles of the feet to increase the arch of the foot without bending the toes. Initially, for those unable to contract the foot muscles, a tape strip will be applied to assist in maintaining the foot in the correct position.

During the exercises, the sacroiliac joints and cervical vertebrae must also be in a neutral position. Participants will be asked to slightly pull in their navel to facilitate the function of the transverse abdominal muscles. Additionally, the chin tuck maneuver will activate the deep neck flexor muscles. The exercises will generally be performed in two phases (static and dynamic).

**Static Phase**

In this phase, the focus will be on pelvic stability through the contraction of the diaphragm, multifidus, pelvic floor, and transverse abdominal muscles to provide a foundation for performing limb movements in subsequent stages. This phase is based on the principle of "proximal stability for distal movements." Progression in this phase will be from standing on two feet, standing on one foot, and then standing in a half-step position.

The support surface will initially be firm and then unstable. Foam, balance pads, rocker boards, and wobble boards will be used. The center of gravity will be challenged by disturbances or weight shifts using elastic bands, and the participant must maintain stability. These positions will elicit automatic postural and reflexive responses.

**Dynamic Phase**

Once the participant can maintain pelvic stability in the previous phase, they will advance to the dynamic phase, where they will perform upper and lower limb movements while maintaining pelvic stability. Progression in this phase will be similar to the static phase: standing on two feet, standing on one foot, and then standing in a half-step position. The support surface will be firm initially and then unstable. In the next stage, the center of gravity will be challenged using elastic bands and ball throws. These exercises will facilitate the retraining of feedforward mechanisms.

Overall, the progression of exercises will be based on each individual's ability, and each stage will be continued until the therapist determines that the patient has achieved the necessary stability and is ready for the next stage of exercises. In these exercises, the focus will be on the quality of performance rather than the quantity of exercises.

**17-2-4. Transcranial Electrical Stimulation**

To apply electrical current, the tDCS device model Neurostim2 from Medina Teb Gostar will be used. Before the patient's arrival, all equipment including electrodes, normal saline, stimulator, cables, elastic bands, and measurement tape will be inspected to ensure they are in good condition and free of defects or damage. The patient will sit on a chair, and the scalp will be examined for any lesions. The researcher will ask the participant to report any skin irritation from the previous session or anything else that would exclude them from the study.

Initially, the electrodes will be placed in sponges soaked with normal saline, and the area of stimulation will be cleaned with alcohol. The electrode size will be 2x4 cm. Stimulation will be applied through two active (anodal) electrodes placed on the scalp. One active electrode will be placed on the M1 region, corresponding to C3 or C4 according to the 10-20 international system. The other active electrode will be placed on the S1 region, which is 2 cm posterior to C3 or C4. Reference (cathodal) electrodes will be placed on the forehead directly above the eyebrow (Figure 6). In general, active electrodes will be placed on the opposite side of the lower back pain, and the reference electrode will be placed on the supraorbital area on the same side as the pain. The device will be set to a current intensity of 1.5 mA for 20 minutes. At the start of stimulation, there will be a 10-second ramp-up period during which the current will gradually increase to 1.5 mA. At the end, there will be a 10-second ramp-down period during which the current will gradually decrease and the device will turn off. Overall, considering the size of the active electrodes, the average current density under these electrodes will be 0.188 mA per square centimeter. The participant will be informed that they might experience a tingling or itching sensation, and the patient will be continuously monitored throughout the treatment. In the sham group, the electrodes will be placed similarly to the intervention group. The device will be turned on, and current will be applied for only 10 seconds, during which the participant will feel a tingling sensation, and then the current will be turned off. The duration of the current application in the sham group will also be 20 minutes (32).

[figure not shown]

Fig 4. Placement of anodal electrodes on S1 and M1 and cathodal electrodes on the supraorbital area

**18. Data Analysis Method**

- All descriptive and statistical analyses will be conducted using SPSS software version 23.
- Descriptive statistics will include the calculation of measures of central tendency (mean) and dispersion (standard deviation).
- The Shapiro-Wilk test will be used to assess the normal distribution of the data.
- To compare baseline (pre-treatment) between the two treatment groups, an Independent t-test with a significance level of 0.05 will be used.
- To examine the effects of within-subject factors (time stages: pre- and post-treatment) and between-subject factors (type of treatment: real transcranial electrical stimulation with sensory-motor exercises vs. sham transcranial electrical stimulation with sensory-motor exercises), a Two-Way Mixed between-within ANOVA will be employed. Effect sizes will be reported using η², and interpreted as small (0.01), medium (0.06), and large (0.14).
- Pearson Correlation will be used to assess the relationship between clinical parameters and neurophysiological parameters related to sensory and motor cortical excitability.

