**4. Analytical Objectives**

**Primary:**

- To compare the average level of lumbar movement control in the groups (intervention and control), between before and after the intervention.
- To compare the average level of lumbar movement control between the groups (intervention and control) before and after the intervention.
- To compare the average level of disability in the groups (intervention and control), between before and after the intervention.
- To compare the average level of disability between the groups (intervention and control) before and after the intervention.
- To compare the average level of pain in the groups (intervention and control), between before and after the intervention.
- To compare the average level of pain between the groups (intervention and control) before and after the intervention.

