**13. Sample Size**

The sample size was calculated using G*Power 3.1.3 software, based on the Jafarzadeh et al. study [28], with pain as the primary outcome measure. The calculation used a between-group Cohen's f of 0.473, a power of 0.8, and an α of 0.05. This power analysis indicated that at least 30 participants were needed. To account for a potential 15% dropout rate, 34 participants were recruited.

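### The planned mixed ANOVA with baseline t-tests is valid but uses the baseline score inefficiently; ANCOVA would raise precision and power at no cost in patients or data

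*Protocol*

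**What the plan says.** Section 17-1 of the protocol (Assessment) sets two measurements per patient: one before the first session and one 24 to 48 hours after the last. Section 18 (Data Analysis Method) then fixes two procedures. The first is a significance test of baseline: "To compare baseline (pre-treatment) between the two treatment groups, an Independent t-test with a significance level of 0.05 will be used". The second is the analysis of the pre and post scores, with time as the within-subject factor and treatment as the between-subject factor: "a Two-Way Mixed between-within ANOVA will be employed". No baseline-adjusted analysis is planned. The section does not say which ANOVA term is the treatment effect, nor what follows if a baseline test is significant.

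Section 4 (Analytical Objectives) lists before-after comparisons within the groups among the primary objectives, for example "To compare the average level of pain in the groups (intervention and control), between before and after the intervention". Each is paired with a between-group comparison.

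Section 13 (Sample Size) sizes the trial "with pain as the primary outcome measure". It continues: "The calculation used a between-group Cohen's f of 0.473, a power of 0.8, and an α of 0.05". The result is 30 patients, raised to 34 for dropout. No SD, mean difference or pre-post correlation is given.

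**The concern.** In a randomised trial with one baseline and one follow-up score, the treatment question is whether the arms differ after treatment, given where the patients started. The planned tests approach this in three unhelpful ways.

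- **The interaction term** is the difference between arms in mean change. It subtracts the whole baseline score, whereas the best linear adjustment (equal SDs) subtracts only the fraction given by the pre-post correlation. The excess adds noise and makes the estimate depend on chance baseline imbalance.
- **The baseline t-test** asks whether an imbalance arose by chance, which randomisation has already answered. It does not adjust the estimate, and in a trial of this size it would miss most imbalances worth adjusting for.
- **The other comparisons** are not treatment effects. The time effect and the within-group changes include the exercise that both arms receive, natural course and regression to the mean. The group main effect averages in a score taken before treatment.

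With 34 patients, precision is scarce, and this loss is avoidable.

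**Working it through.** **Inputs.** From Section 13: f = 0.473, alpha 0.05, power 0.80, 30 evaluable patients (15 per arm), 34 recruited (17 per arm). From Sections 17-1 and 17-2: two assessments and two arms in balanced blocks. Assumed, because the protocol is silent: pre-post correlation ρ of 0.3, 0.5 and 0.7; equal SD σ before and after; and, for power only, f read as a post-treatment difference d = 2 × 0.473 = 0.946 SD.

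**Step 1: the plan's own figure.** Section 13 says "This power analysis indicated that at least 30 participants were needed". A repeated-measures between-factors F test with m = 2 measurements and ρ = 0.5 has noncentrality f²·N·m/(1+(m−1)ρ) = 0.2237 × 30 × 2/1.5 = 8.95 on (1, 28) df. Its power is 0.823, and 30 is the smallest even N that reaches 80%. A one-sided two-group t-test also gives 30 (power 0.811). A two-sided two-group comparison gives 38, with power 0.706 at N = 30. The figure can therefore be reproduced, but the match does not settle which contrast f describes.

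**Step 2: precision.** Variance per patient is 2(1−ρ)σ² for the change score and (1−ρ²)σ² for ANCOVA. The ratio is 2/(1+ρ).

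| ρ | change, 2(1−ρ) | ANCOVA, 1−ρ² | ratio |
|---|---|---|---|
| 0.3 | 1.40 | 0.91 | 1.54 |
| 0.5 | 1.00 | 0.75 | 1.33 |
| 0.7 | 0.60 | 0.51 | 1.18 |

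Estimating the baseline slope multiplies the ANCOVA variance by 1 + 1/(N−4) = 1 + 1/26 = 1.038 at N = 30. The ratios then become 1.48, 1.28 and 1.13. The advantage disappears only when (1+ρ)/2 × 1.038 exceeds 1, that is, above ρ of about 0.93.

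**Step 3: chance imbalance.** At 17 per arm the SE of the baseline difference is √(2/17) = 0.343 SD. The change-score estimate carries (1−ρ) times that difference, with opposite sign. For a one-SE imbalance this is 0.7 × 0.343 = 0.24, 0.5 × 0.343 = 0.17 and 0.3 × 0.343 = 0.10 SD.

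**Step 4: the baseline t-test.** For a true-sized imbalance of 0.5 SD, noncentrality is 0.5/0.343 = 1.46 on 32 df, so power is 29%. A non-significant result gives little reassurance.

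**Step 5: power at N = 30, two-sided 0.05.** Noncentrality is d/√(v × 2/15). For the interaction, v = 2(1−ρ) on 28 df. For ANCOVA, v = (1−ρ²) × 1.038 on 27 df.

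| ρ | interaction: noncentrality, power | ANCOVA: noncentrality, power |
|---|---|---|
| 0.3 | 2.19, 56% | 2.67, 73% |
| 0.5 | 2.59, 71% | 2.94, 81% |
| 0.7 | 3.34, 90% | 3.56, 93% |

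A simulation of 20,000 trials per row gave 56/71/90% and 73/81/93%. If all 34 patients are evaluable, the figures are 62/76/93% and 79/86/96%.

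**Step 6: the group main effect.** With no true baseline difference its effect is d/2 and v = (1+ρ)/2. At ρ = 0.5 and N = 30, power is 30%. If this term were taken as the treatment test, most of the signal would be lost.

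**The case against.** The strongest reply is that nothing here is wrong in the sense of invalid. Under randomisation the interaction estimate is unbiased and its test holds its error rate. Chance imbalance is already reflected in its standard error. This stands: a reader might infer from Step 3 that the planned estimate is biased, but the shift is conditional error in the particular sample, not bias over randomisations.

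A reader might also infer that ANCOVA restores the stated 80% power. The documents do not support that. No correlation is given. At N = 30 ANCOVA stays below 80% at ρ = 0.3 to 0.4 (73 to 76%), while from about 0.6 the interaction already has about 80%. The switch crosses the 80% line only between about 0.5 and 0.6. All the power figures also depend on reading f as a post-treatment difference, which Section 13 does not say. Read as the interaction effect in the software's own terms, f = 0.473 would need only 12 patients at ρ = 0.5, and there would be no shortfall.

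The within-group objectives do not show that a before-after change will be reported as a tDCS effect. Section 4 pairs each with a between-group objective, and Section 6 frames the conclusion as a difference between groups. Naming the confirmatory term may also be left to an analysis plan that is not shown. Regression to the mean after entry at pain of 4 or more is a reason not to interpret within-group change, but it affects both arms alike and does not favour ANCOVA over change scores.

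Finally, Section 13 says that patients were recruited, so data may already exist. That affects how the change is documented, not whether the text should be improved.

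**Conclusion.** The point holds as a recommendation on efficiency and clarity. The protocol fixes a valid analysis that is less precise than ANCOVA. The variance ratio is 1.54/1.33/1.18 at correlation 0.3/0.5/0.7, slightly less after the small-sample term, and it assumes only equal SDs before and after. A one-SE chance imbalance moves the observed estimate by 0.24/0.17/0.10 SD at 17 per arm. The baseline tests serve no purpose, and the main effects and within-group changes do not estimate the treatment effect.

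The gain of about 17, 10 and 3 percentage points of power at N = 30 is conditional on d = 0.946 SD after treatment and on a correlation that the protocol does not state. It should be presented as a range, not as recovery of the planned power.

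**What to change.** In Section 18 of the protocol:

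- For pain, disability, movement control and each neurophysiological outcome, make the treatment test an ANCOVA of the post-treatment score on arm plus baseline score. Report the adjusted mean difference with its 95% CI. Effect sizes as η² may be kept alongside.
- Delete the baseline significance tests and present baseline means and SDs by arm.
- State that the arm coefficient is the test of treatment. Label within-group changes, in Section 4 as well, and any ANOVA main effects as descriptive.
- In Section 13, state the assumed pre-post correlation and the contrast to which f = 0.473 refers.

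The cost is one degree of freedom and some wording, with the same patients, visits, data and SPSS software. If outcome data have already been examined by arm, record the change as a dated amendment and report the mixed ANOVA beside it.

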**Secondary:**

- To compare the average amplitude of N80 and N150 in the groups (intervention and control), between before and after the intervention.
- To compare the average amplitude of N80 and N150 between the groups (intervention and control) before and after the intervention.
- To compare the average active motor threshold of the multifidus and transverse abdominis muscles in the groups (intervention and control), between before and after the intervention.
- To compare the average active motor threshold of the multifidus and transverse abdominis muscles between the groups (intervention and control) before and after the intervention.
- To compare the average amplitude of the motor-evoked potentials (MEPs) of the multifidus and transverse abdominis muscles in the groups (intervention and control), between before and after the intervention.
- To compare the average amplitude of the motor-evoked potentials (MEPs) of the multifidus and transverse abdominis muscles between the groups (intervention and control) before and after the intervention.
- To examine the correlation between clinical parameters and brain neurophysiological parameters.

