**5. Research Questions and Hypotheses**

- Is there a difference in the average amplitude of N80 and N150 in the groups (intervention and control) between before and after the intervention?
- Is there a difference in the average amplitude of N80 and N150 between the groups (intervention and control) before and after the intervention?
- Is there a difference in the average active motor threshold of the multifidus and transverse abdominis muscles in the groups (intervention and control) between before and after the intervention?
- Is there a difference in the average active motor threshold of the multifidus and transverse abdominis muscles between the groups (intervention and control) before and after the intervention?
- Is there a difference in the average amplitude of the motor-evoked potentials (MEPs) of the multifidus and transverse abdominis muscles in the groups (intervention and control) between before and after the intervention?
- Is there a difference in the average amplitude of the motor-evoked potentials (MEPs) of the multifidus and transverse abdominis muscles between the groups (intervention and control) before and after the intervention?
- Is there a difference in the average level of lumbar movement control in the groups (intervention and control) between before and after the intervention?
- Is there a difference in the average level of lumbar movement control between the groups (intervention and control) before and after the intervention?
- Is there a difference in the average level of disability in the groups (intervention and control) between before and after the intervention?
- Is there a difference in the average level of disability between the groups (intervention and control) before and after the intervention?
- Is there a difference in the average level of pain in the groups (intervention and control) between before and after the intervention?
- Is there a difference in the average level of pain between the groups (intervention and control) before and after the intervention?
- Is there a significant correlation between clinical parameters and brain neurophysiological parameters?

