**7. Novelty of the Study**

Studies indicate that tDCS and sensory-motor exercises may positively affect pain reduction in patients with chronic low back pain. However, as noted, sensory and motor processing in the brain is disrupted in these patients. This aligns with other behavioral evidence indicating issues in sensory-motor control of the back in these individuals, which can ultimately lead to disability. Sensory-motor control is considered a key factor in the progression and recurrence of low back pain. Despite the significance of brain changes in sensory and motor areas and disruptions in sensory-motor control, no study has yet examined the effects of anodal tDCS on sensory and motor areas combined with sensory-motor exercises on brain processing and improvement in sensory-motor control in these patients. This study aims to assess for the first time the impact of anodal tDCS on the M1 and S1 regions, combined with exercises, on improving the mentioned parameters. The goal is to determine whether stimulating these regions with anodal tDCS, combined with exercises, can be a more effective treatment for individuals with chronic low back pain, considering the decreased excitability of the M1 and S1 areas in these individuals. The study will also focus on neurophysiological parameters in addition to clinical parameters, seeking to uncover potential mechanisms and understand the relationship between improvements in clinical parameters and changes in neurophysiological parameters, which has not been addressed before.

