**17-1. Assessment**
Assessments will be performed before the first treatment session and 24 to 48 hours after the completion of the treatment. Two laboratory tests and one clinical test will be conducted, and two questionnaires will be completed.

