**17-1-1-1. Test for Brain Sensory Processing**
To assess brain sensory processing, sensory evoked potentials will be recorded using the EMG/NCV/EP5000 Q device. Generally, sensory evoked potentials evaluate the sensory nervous system by applying somatosensory stimuli to record brain waves using electroencephalography electrodes. Electroencephalography reflects the brain's spontaneous electrical activity over a short period, whereas sensory evoked potentials are not recorded spontaneously but are associated with pre-stimulation.

In this test, two variables (amplitude N80 and N150) will be analyzed. Electrophysiological research shows that sensory evoked potentials recorded by electroencephalography reflect the processing of afferent sensory pathways in distinct areas of the brain cortex. The N80 time window is believed to represent processing in the primary sensory cortex (S1), while the N150 time window reflects processing in the secondary sensory cortex (S2).

For the test, participants will sit comfortably on a chair with their feet on the ground and hands relaxed. Participants will be asked to sit with their eyes closed but remain awake during the test. Sensory evoked potentials will be recorded using surface electrodes placed on the scalp. These electrodes will be positioned on the S1 area, 3 centimeters lateral to Cz and 2 centimeters posterior, and on the opposite side of the participant’s pain location. The scalp at the recording site should not have more than 5 kilo-ohms resistance. The reference electrode will be placed at Fz and the ground electrode on the forehead.

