**17-1-1-2. Test for Brain Motor Processing**

To assess brain motor processing, motor threshold and motor evoked potentials will be measured using the TMS MagPro X100 device. Generally, the goal of motor evoked potentials is to evaluate the motor nervous system by applying a single stimulating pulse through transcranial magnetic stimulation to the motor cortex and then recording this motor stimulation from the corresponding muscle using electromyography electrodes. The recorded wave is known as the motor evoked potential.

Motor threshold will also be an index of cortical excitability and will be used to determine the intensity of stimulation with the device.

In this test, four variables (active motor threshold and amplitude of motor evoked potentials for the multifidus muscle and abdominal transverse) will be examined. These variables are indicators of excitability, performance, and the integrity of neural pathways and corticospinal areas related to these muscles.

For recording variables related to the multifidus muscle, the patient will sit comfortably on a chair with their feet on the ground. A surface electromyography electrode will be placed on the spinous process of L5, aligned with a line connecting the PSIS and the L1-L2 space. The ground electrode will be placed on the iliac crest. The bandwidth will be set from 5 to 500 Hz. To achieve maximal contraction in the multifidus muscle, the participant will be asked to perform a trunk extension against resistance and hold it for 3 seconds. This movement will be repeated 3 times, and the maximum contraction will be measured based on the Root Mean Square (RMS) within a 1-second window. Then, 20% of this value will be used as the submaximal contraction, which will be displayed on a monitor for the participant to maintain throughout the recording. This contraction is intended to facilitate the recording of motor evoked potentials in the paravertebral muscles. In other words, if the muscle is in a resting state, recording will be difficult.

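### Section 18 plans a plain Pearson correlation that does not say it uses changes and takes no account of arm, so it does not secure the improvement-versus-change aim of section 7

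*Protocol*

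**What the plan says.** Protocol section 7 (Novelty of the Study) states the mechanistic aim as a relation between two changes: to "understand the relationship between improvements in clinical parameters and changes in neurophysiological parameters".

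The formal statements are looser. The last secondary objective in section 4 is "To examine the correlation between clinical parameters and brain neurophysiological parameters", and section 5 turns it into a yes/no question: "Is there a significant correlation between clinical parameters and brain neurophysiological parameters". Neither mentions change.

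Section 18 (Data Analysis Method) fixes the method: "Pearson Correlation will be used to assess the relationship between clinical parameters and neurophysiological parameters related to sensory and motor cortical excitability". It does not say which values are correlated, whether the arms are pooled, separated or adjusted for, or what significance level applies. The 0.05 in that section belongs to the baseline t-test.

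The parameters are countable. The primary objectives list three clinical ones: movement control, disability and pain. Section 17-1-1-1 gives two sensory ones ("In this test, two variables (amplitude N80 and N150) will be analyzed"), and section 17-1-1-2 gives four motor ones ("four variables (active motor threshold and amplitude of motor evoked potentials for the multifidus muscle and abdominal transverse) will be examined").

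**The concern.** The sentence in section 18 permits several analyses that answer different questions. A baseline correlation says nothing about improvement. A correlation of post-treatment or change values over both arms together combines two things: whether patients who change more on one measure change more on the other, and whether the arms differ on both. If stimulation moves both kinds of measure, the second part alone produces a correlation, even when patients within an arm show none. Only a change-on-change analysis that accounts for arm isolates the patient-level relation that section 7 describes.

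At stake is the mechanistic reading of the trial. Section 5 settles the question by significance and names no particular pair, so any one of 18 could be reported as a yes. The arm artefact is largest when the treatment works on both kinds of measure, which is also when a mechanism would most naturally be claimed. The primary group comparisons are not affected.

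**Working it through.** **Inputs.** Section 13 gives Cohen's f "of 0.473, a power of 0.8, and an α of 0.05", at least 30 participants needed and 34 recruited. Section 17-2 gives two groups in balanced blocks of 4, taken as 1:1. Assumptions, because the protocol is silent: 0.05 for each correlation; arms pooled without adjustment; and, for the arm artefact, the planned pain effect applied to the other measures too.

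**1. The plan's own figure.** N = 30 reproduces as a between-group effect in a repeated-measures ANOVA with 2 groups, 2 measurements and an assumed correlation of 0.5 between measurements. The noncentrality is f² x N x m / (1 + (m - 1) x rho) = 0.473² x 30 x 2 / 1.5 = 8.95, which gives power 0.823. N = 28 gives 0.794. For two equal groups d = 2f = 0.946. The protocol gives no figure for the correlations themselves.

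**2. Number of pairs.** 3 clinical x (2 + 4) neurophysiological = 18 for one set of values, or 36 if run at both time points.

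**3. False positives with no arm effect and no true link.** Expected number: 18 x 0.05 = 0.9. Chance of at least one if the tests were independent: 1 - 0.95^18 = 0.60. The measures within each set will be correlated, which lowers this. In simulation (20,000 runs) the chance is about 0.55, 0.46 and 0.34 for within-set correlations of 0.3, 0.5 and 0.7. The range is 34% to 60%.

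**4. Correlation created by pooling arms.** With equal arms, unit within-arm variance, arm differences dc and dn, and zero within-arm association:

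r = (dc x dn / 4) / sqrt((1 + dc²/4)(1 + dn²/4))

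For dc = dn = 0.946: 0.2237 / 1.2237 = 0.18. For dc = dn = 0.5: 0.0625 / 1.0625 = 0.06. The correlation is negative if the two measures move in opposite directions; the size is the same. The critical |r| at two-sided 0.05 is 0.361 for N = 30 and 0.339 for N = 34.

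Simulated rejection rate per test:

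| Shift, clinical / neurophysiological (SD) | Induced r | Pooled, N = 30 | Pooled, N = 34 | Adjusted for arm |
|---|---|---|---|---|
| 0 / 0 | 0 | 5% | 5% | 5% |
| 0.946 / 0 | 0 | 5% | 5% | 5% |
| 0.5 / 0.5 | 0.06 | 6% | 6% | 5% |
| 0.946 / 0.5 | 0.10 | 9% | 9% | 5% |
| 0.946 / 0.946 | 0.18 | 17% | 18% | 5% |

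In the last row about 3 of 18 tests are expected to be significant (18 x 0.165 = 3.0 at N = 30). The chance of at least one is 0.56 to 0.94 at N = 30, depending on the within-set correlations.

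**5. After the fix.** Adjusting for arm returns each test to 5% whatever the arm effect, but the chance of at least one false positive among 18 stays at 0.34 to 0.60. Adding a Bonferroni limit of 0.05/18 = 0.0028 brings it to 0.03 to 0.05. For scale, that limit raises the critical |r| of a plain correlation to 0.527 at N = 30.

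**The case against.** The strongest reply is that this turns silence into error. Section 18 does not tell anyone to pool arms, use raw levels or test at 0.05. Separate correlations within each arm would fit the sentence and avoid the arm artefact. The formal objective and research question do not mention change, so Pearson correlation does answer them as worded. Multiplicity for a secondary analysis usually belongs in a statistical analysis plan, which is not available here. And if treatment shifts both measures, the pooled correlation really exists in the studied population; it is false only as evidence of a patient-level link.

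Much of this stands. A reader might infer that the plan fails to analyse changes, or that it will manufacture significant links. The protocol supports neither: change scores and per-arm analysis are not excluded, and the artefact needs sizeable arm effects on both variables. It is close to nominal at 0.5 SD on both, and absent if treatment moves only one side or if baseline values are used. The effect of 0.946 was planned for pain alone; no effect is given for any neurophysiological measure. A false positive somewhere being more likely than not, absent any arm effect, also holds over only part of the 34% to 60% range. Missing multiplicity adjustment would not be a finding by itself.

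What the reply does not remove is the gap between sections 7 and 18. The protocol states an aim about changes, poses a significance question, names the test, and leaves open the choices that decide whether the test addresses the aim. Per-arm analysis is also a weak way out: 15 patients per arm put the critical |r| at 0.514 and double the tests to 36.

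**Conclusion.** The point holds as a mismatch and an under-defined method, not as an analysis that is certain to mislead. Section 18 does not ensure an answer to the aim in section 7, and one permitted reading, pooling post-treatment or change values, confounds the treatment effect with patient-level association. On that reading the per-test false-positive rate runs from 5% (no effect on at least one side) through about 6% (0.5 SD on both) to 17-18% (0.946 SD on both). These figures assume 0.05 per test, 1:1 arms and no within-arm association. Separately, 18 unranked pairs carry a 34% to 60% chance of at least one false positive without any arm effect, so a yes to the section 5 question would be weak evidence of mechanism. This is a worthwhile, inexpensive improvement to a secondary analysis; the primary comparisons are untouched.

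**What to change.** Replace the correlation sentence in section 18 with text to this effect: for each of the 18 pairs, the pre-to-post change in the clinical measure is related to the pre-to-post change in the neurophysiological measure by partial correlation given arm. Use a rank-based version for movement control, which is a count from 0 to 6. Report all 18 estimates with 95% confidence intervals. Either label the set exploratory, with no claim of mechanism from a single unadjusted p-value below 0.05, or adjust across the 18, for example by Holm or Benjamini-Hochberg. Align the objective in section 4 and the question in section 5 with the same wording about changes.

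The cost is wording, a small amount of analysis work and one degree of freedom for arm. No new data are needed, since both assessments are already planned. The drawback to accept is fewer nominally significant correlations.
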